## Abstract

**Background:**

Keloids are a burden for patients due to physical, aesthetic and social complaints and treatment remains a challenge because of therapy resistance and high recurrence rates. The main goal of treatment is to improve the quality of life (QoL); this implies that, apart from surgical outcomes, patient-reported outcome measures (PROMs) need to be taken into account. Decision making in keloid treatment is difficult due to heterogeneity of the condition and the lack of comparative studies.

**Methods/Design:**

This is a multicentre, randomised controlled open trial that compares 1) intralesional cryotherapy versus excision and corticosteroids for primary keloids, and 2) intralesional cryotherapy versus excision and brachytherapy for therapy-resistant keloids. The primary outcome is the Patient and Observer Scar Assessment Scale (POSAS), a 12-item scale (with score 12 indicating the best and 120 indicating the worst scar imaginable). A difference of six points on the total score is considered to be of clinical importance. Secondary outcomes are recurrence rates, volume reduction, Skindex-29 scores, SF-36 scores and complication rates. Primary and secondary outcome measurements are taken at baseline, and at 2, 12, 26 and 52 weeks postoperatively. For analysis, a linear mixed model is used. A total of 176 patients will be included over a period of 2.5 years. The protocol is approved by the Medical Ethics Committee of the Erasmus University Medical Centre Rotterdam and follows good clinical practice guidelines.

**Discussion:**

The outcomes of this study will improve evidence-based decision making for the treatment of keloids, as well as patient education.

**Trial registration:**

Dutch Trial Register NTR4151.

## Background

Keloids are pathologic scars that grow beyond wound borders and act as a benign tumour. The physical, aesthetic and psychological complaints that they cause are of great concern [1,2].

After injury, the skin heals by forming a scar. Dysregulation of signalling molecules in the complex healing process can result in keloid formation, with several times more collagen synthesis than for normal skin and normotrophic scars, and a higher ratio of type 1 to type 3 collagen [3-7]. The aetiology of keloids remains unknown. Although it is suggested that a relation exists with wound tension, sex hormones, sebaceous gland activity, melanocyte concentration and overlying keratinocytes, as well as with genetic predisposition, no single theory has proven of value in all aspects of keloids [8-12]. The highest incidence is seen in patients with a dark skin tone, whereas Mediterraneans, South Americans, and Asians are slightly less affected, and Caucasians are the least affected (<1%) [1,8,13]. It was shown that scars give acceptability problems (91%) and influence social functioning (82%) in a mixed group of scar types that were mainly on visible body sites[2]. At least as much problems can be expected for patients with keloids, as keloids are often visible on earlobes or so large that they are visible through clothing. Besides this major psychosocial burden, keloids give rise to pain and pruritus in 80% of keloid patients [1,2].

Treatment of keloids is challenging because of therapy resistance and high recurrence rates, resulting in the search for more treatment options for keloids. Over decades, systematic reviews included zero to only three randomised controlled trials per treatment option, with a lot of heterogeneity between the studies [1,14,15]. In the absence of sufficient numbers and methodologically sound randomised trials, no consensus for a treatment of first choice has been reached.

In our clinical practice a ‘stepped-care approach’ is generally used; that is, initially, the least invasive and safest treatments are used, which are changed to more radical treatments in case of resistance or recurrence.

Because keloid is a benign condition, the main treatment goal should be to relieve the burden, which consists mainly of pruritus, pain and aesthetic complaints; all these are subjective symptoms. To objectively measure subjective burden (that is, in a reproducible way) the effects of the treatment options should be assessed using validated scar assessment scales and patient-reported outcome measures (PROMs), in addition to surgical results such as volume reduction, recurrence and complication rates.

In our centre, the ‘stepped-care approach’ implies that the first step is generally conservative treatment with corticosteroid injections. Other conservative methods, like laser therapy and silicone occlusive dressings, have not proven to achieve patient satisfaction in keloid treatment as is clear from recent systematic reviews [14-17]. If keloids are of such a size that conservative treatment may not be sufficient, the next step is surgical treatment.

Because excision as monotherapy gives a recurrence rate of ≥70%, an adjuvant treatment should be used. The most frequently used adjuvants are corticosteroid injections, pressure therapy and brachytherapy (interstitial radiotherapy) [14,18]. Another surgical keloid treatment option that gained popularity some years after several case series were published, is intralesional cryotherapy [19-21]. As no trials have compared intralesional cryotherapy with established conventional therapies, we aimed to explore the position of intralesional cryotherapy in the ‘stepped-care approach’.

### Objectives

Beginning in November 2012, we initiated a randomised clinical trial in which we compare frequently used keloid therapies in the Netherlands: excision and intralesional steroid injections, excision and brachytherapy, and intralesional cryotherapy. Outcomes are surgical results and PROMs. The results will assist in producing a better ‘evidence-based’ treatment algorithm for keloid patients.

## Methods/Design

### Trial design

The design is a multicentre, randomised controlled open trial, which used minimisation to control for skin type, location and duration of disease. The trial consists of two parts: one for primary keloids and one for resistant keloids. Primary keloids are keloids that have not been surgically treated and, to some extent, have responded to corticosteroids. Resistant keloids are keloids that recurred after excision or those that did not respond to corticosteroids (progression within six weeks after corticosteroid injection).

For the primary keloids we randomise between either intralesional cryotherapy or excision and additional corticosteroids. The resistant keloids are randomised between either intralesional cryotherapy or excision and brachytherapy. Follow-up assessments are in weeks 2, 12, 26, and 52 post-treatment. The follow-up period is based on scar maturation, which lasts about one year, and the chance of recurrence that usually occurs within the first year [22,23].

### Patient recruitment

Patients who present with a keloid at an outpatient clinic of the four participating centres are considered for the study. A keloid is a clinical diagnosis and is distinguished from hypertrophic scars by the clinician’s judgement. The judgement between hypertrophic scars and keloid is based on: the growth history, starting early versus late after trauma, remaining stable versus still growing; shape, following initial lesion versus not following the initial lesion; and size, <0.5 cm versus >0.5 cm beyond the original lesion.

At a later stage, we will report how many patients with keloids were seen and how many were eligible for the study. Inclusion criteria are:

1. Keloid with a surgical indication.

2. One to three keloids that can be treated in one session.

3. Minimal size of 1 × 1 cm.

4. Suitable for excision and primary closure.

5. Patient aged between 18 and 75 years.

6. Fully mentally competent.

7. Sufficient knowledge of the Dutch or English language.

Exclusion criteria are:

1. Hypertrophic scars.

2. Scars after burn wounds.

3. Keloids less than one year old.

4. Pregnancy.

5. Use of systemic chemotherapeutics or chronic use of systemic corticosteroids or immunosuppressive medication.

6. Hypersensitivity for local anaesthetics, adrenaline, or triamcinolone (primary keloids).

7. Patients not sufficiently fit for brachytherapy (resistant keloids).

8. Severe comorbidity with life expectancy under one year.

### Consent procedure

At the first outpatient visit, eligible patients are informed about the study by a member of the research staff and written information is provided. After a consideration period of at least two weeks, the patient is contacted and registered in the study database when the patient wants to participate. Before treatment, a witnessed, written informed consent is obtained from all participants, following the guidelines of the local ethical committee.

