### Randomisation (treatment allocation)

Previous studies on keloid treatment showed that specific characteristics are predictors of recurrence. Therefore, we want to assure homogeneity between treatment groups regarding these characteristics, such as duration of the keloid existence (dichotomous; <5 years or ≥5 years) and location of the keloid (categorical; sternal region, auricular region and other). In addition, we try to match for skin type because of the strong association with the development of keloids, but the doubtful relation with recurrence rate (categorical; Fitzpatrick type 1 and 2, type 3 and 4, type 5 and 6). Because of the many different strata that would be formed and considering the total number of patients to be included, we choose not to use permuted blocks but will use the more sophisticated technique of minimisation. We will minimise on the three factors previously mentioned. The allocation of a new subject is determined by the allocation of the subjects already enrolled. We apply a 20% random chance factor to keep allocation predictability at a minimum. The software used is the open source program MinimPy (http://minimpy.sourceforge.net/).

When a patient agrees to participate in the study they irrevocably receive a unique identification number, which cannot be changed or removed from the database. After completion of baseline measurements, treatment allocation is conducted through a central computerized allocation using the locked database for all participating centres. Then the physician and the patient are informed of the assigned condition and the treatment is planned. In this way, allocation concealment is guaranteed.

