### Blinding

Neither physicians nor patients are blinded for treatment. They cannot be blinded due to surgery under local anaesthesia and differences in postoperative selfcare instructions. Furthermore, during the follow-up assessments, a physician or layperson would immediately recognize the treatment type by the resulting wound or scar.

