### Data collection

Data are collected at baseline, before randomisation, and at follow-up assessments 2, 12, 26, and 52 weeks after treatment. The questionnaires are preferably filled out online, although a paper version is also available. All paper questionnaires are scanned and stored on a secure disk. The online questionnaires are saved by the online questionnaire program, and a backup is made regularly.

Photographs are taken at all visits. Volume of the keloid is measured at baseline and after the skin has completely healed at 12, 26, and 52 weeks after treatment.

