### Statistical analysis

Baseline demographic and clinical characteristics will be presented as proportions or means and standard deviations (SD) where appropriate. Because of the longitudinal data with multiple influencing factors, a sophisticated model is necessary. Mixed models (also called multilevel linear regression analysis) is a technique that efficiently uses longitudinal data and can work with patients’ data even though measures at certain time points may be missing.

The units of analysis are the repeated measurements of the patient (first level), not the keloid, because we use several QoL measures that are not measurable for the unit keloid. The second level will be the individuals participating in the study. If necessary, a third level of subgroups with specific characteristics (skin type, duration of keloid disease and location of the keloid) can be added. If the third level is shown to improve the fit of the model, it will be incorporated in the model. We will use backward elimination and start with an unstructured covariance structure for intercept and time (slope). Simplifications of the random part of the model will be tested using the deviance statistic with restricted maximum likelihood. For the fixed part we will postulate a saturated model. We take in account time, logarithm of time and squared time, treatment condition and its interactions with time. Nonsignificant effects will be excluded using Wald tests. The fit of the final fixed model will be compared with the saturated model and will be checked using ordinary maximum likelihood. When characteristics like sex, age, skin type, duration of keloid disease and location of the keloid make a significant contribution to the model, they will be incorporated in the model [34-37]. Differences between treatment effects will be expressed in terms of effect sizes, standard errors and *P* values. Effect sizes will be calculated by dividing the estimated differences by the estimated standard deviation. An effect size of 0.20 is considered a small effect, 0.50 a medium effect and 0.80 as a large effect [38].All analyses will be performed on an intention-to-treat basis. IBM SPSS version 21.0 and SAS version 9.3 will be used to perform the analyses.

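### Written consent is required only before treatment, so as written a patient in this open trial may sign, or decline to sign, already knowing the allocated arm

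*Protocol article*

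**What the plan says.** The Consent procedure section describes information at the first visit and at least two weeks to consider. After that "the patient is contacted and registered in the study database when the patient wants to participate". The signature has its own, later limit: "Before treatment, a witnessed, written informed consent is obtained from all participants". The same sentence refers to the guidelines of the local ethical committee.

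The Randomisation (treatment allocation) section gives the order of events. On agreeing to take part, patients enter the database permanently: "they irrevocably receive a unique identification number, which cannot be changed or removed from the database". Next, "After completion of baseline measurements, treatment allocation is conducted through a central computerized allocation". After that, "Then the physician and the patient are informed of the assigned condition and the treatment is planned". The section concludes that allocation concealment is thereby guaranteed.

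Three other statements bear on the point:
- Blinding: "Neither physicians nor patients are blinded for treatment".
- Data collection: "Data are collected at baseline, before randomisation, and at follow-up assessments 2, 12, 26, and 52 weeks after treatment".
- Statistical analysis: "All analyses will be performed on an intention-to-treat basis".

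**The concern.** The decision to enter a randomised trial should be binding before the arm is known. Here the article gives both a deadline for the signature and a sequence of events, and the deadline is tied to treatment, the last event in the sequence. Registration depends on the patient wanting to take part, and allocation depends on completed baseline measurements. Neither is made conditional on a signature.

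The arms are very different experiences: cryotherapy against excision with steroid injections for primary keloids, and cryotherapy against excision with brachytherapy for resistant keloids. A patient who has not yet signed may accept one and refuse the other. If those who refuse differ in prognosis from those who stay, the patients with outcome data are no longer the groups that were randomised. Central allocation does not protect against this, because the selection occurs after the assignment has been revealed. The same wording also permits baseline study measurements before written consent.

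**Working it through.** **Order of events as written**

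1. The patient is informed and has at least two weeks to consider (Consent procedure).
2. The patient wants to participate and is registered (Consent procedure), with a permanent number (Randomisation).
3. Baseline measurements are completed (Randomisation; Data collection).
4. Central allocation is run (Randomisation).
5. Physician and patient are told the arm, and treatment is planned (Randomisation).
6. Treatment is given. Written consent must exist by this point (Consent procedure).
7. Visits follow at 2, 12, 26 and 52 weeks, counted from treatment (Trial design; Data collection).

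A signature at any point from step 1 up to just before step 6 meets the stated rule. Signing after step 5 is therefore allowed, though not prescribed.

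**What happens to a patient who declines after step 5**

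The permanent number and the intention-to-treat statement keep the patient allocated. Without treatment, the visits in step 7 have no starting date. The Intralesional cryotherapy section says follow-up continues as planned, but in the context of a treatment that was not effective. The Sample size section says that no withdrawal rules have been specified. The mixed model accepts missing time points, but a patient with baseline data alone adds almost nothing to the post-treatment contrast. Without a signature, even the baseline data may not be usable.

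**Possible shift in one arm's mean (assumed inputs)**

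Let a fraction f of one arm decline, and let those patients differ by D points from those who stay. The full-arm mean is (1 − f)·m + f·(m + D) = m + f·D, where m is the mean of those who stay. The observed mean is m, so the shift is f × D in size. The documents give neither f nor D. The top value of D is one SD, about 15 points (Sample size calculation).

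| f | D = 5 | D = 10 | D = 15 |
|---|---|---|---|
| 5% | 0.25 | 0.5 | 0.75 |
| 10% | 0.5 | 1.0 | 1.5 |
| 20% | 1.0 | 2.0 | 3.0 |

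Against the 6-point difference in the Outcomes section, the 10% row runs from 0.5/6 = 8% to 1.5/6 = 25%.

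**Effect on power**

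The plan's own figures reproduce. With SD 15 and correlation 0.75, the SD of change is 15 × √(2 × (1 − 0.75)) = 10.6. The standardised difference is 7.5/10.6 = 0.707, for which a two-sided t-test at 0.05 with 80% power needs 33 per group. Then 33/0.75 = 44, and 44 × 4 = 176. Two-sided testing is assumed, as the article does not state it.

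If refusal came on top of the planned 25% loss, 44 × 0.75 × (1 − f) patients per group would remain. For f = 0, 5%, 10% and 20% that is 33.0, 31.3, 29.7 and 26.4. Power by normal approximation is about 82%, 80%, 78% and 73%. The fix changes no sample size.

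**The case against.** Three stronger readings are tempting, and the article supports none of them.

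- A reader might infer that consent is taken after the arm is disclosed. The stated limit is equally met by signing at registration or before baseline, and the Randomisation section has the patient agreeing to participate before allocation.
- A reader might infer that patients who decline drop out of the intention-to-treat comparison. The permanent number and the intention-to-treat statement say otherwise. What is exposed is their outcome data, not their membership of the analysis set.
- A reader might infer that untreated patients are not followed. The article is silent, and a full protocol could cover them. Timing visits from treatment is also natural for outcomes tied to wound healing and scar maturation.

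It can further be said that the consent sentence defers to ethics committee guidelines, that the Safety concerns section cites good clinical practice and Dutch legislation, and that a condensed article need not give the day of signature. Patients have two weeks to consider, and 25% loss is already allowed for. A patient who has signed can still withdraw on learning the arm.

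Most of this stands as a limit on how far the point reaches. It does not remove the point. The article does not merely omit the timing: it states a deadline and ties it to an event that follows disclosure. General references to guidelines do not replace that deadline. The 25% allowance protects sample size, not comparability, if losses differ by arm.

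**Conclusion.** The point holds as a badly placed rule. The stated deadline permits written consent, or its refusal, after the arm is known. It does not show that this occurs in practice.

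The consequence is possible arm-dependent loss of post-treatment data. Its size cannot be derived from the documents. At an assumed 10% refusal confined to one arm, with a 5 to 15 point difference, the shift is 0.5 to 1.5 points. The upper value requires those who decline to differ by a full SD. Similar refusal by similar patients in both arms would largely cancel in the treatment difference, leaving mainly the loss of power. The figures describe raw arm means; a mixed model that keeps these patients' baseline scores might recover part of the shift.

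The point merits correction because the remedy is simple and the wording also touches on consent for baseline measurements.

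**What to change.** - In Consent procedure and in Randomisation, state that signed consent precedes baseline measurements. Make the consent date a mandatory entry before the allocation program can be run.
- State that every allocated patient is counted by arm, including those who decline or are not treated. Where their consent allows, assess untreated patients at visits timed from the allocation date.
- Recruitment was already under way when the article was submitted (Trial status), so compare consent dates with baseline and allocation dates for patients already enrolled. Report any signatures obtained after allocation, by arm.

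The cost is a few sentences and one check at the allocation step. No extra visit is needed before allocation, since baseline measurement already precedes it. Following untreated patients adds a few assessments. Earlier consent reduces refusal after disclosure but does not remove it, so the second item is needed as well as the first.

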### Randomisation (treatment allocation)

Previous studies on keloid treatment showed that specific characteristics are predictors of recurrence. Therefore, we want to assure homogeneity between treatment groups regarding these characteristics, such as duration of the keloid existence (dichotomous; <5 years or ≥5 years) and location of the keloid (categorical; sternal region, auricular region and other). In addition, we try to match for skin type because of the strong association with the development of keloids, but the doubtful relation with recurrence rate (categorical; Fitzpatrick type 1 and 2, type 3 and 4, type 5 and 6). Because of the many different strata that would be formed and considering the total number of patients to be included, we choose not to use permuted blocks but will use the more sophisticated technique of minimisation. We will minimise on the three factors previously mentioned. The allocation of a new subject is determined by the allocation of the subjects already enrolled. We apply a 20% random chance factor to keep allocation predictability at a minimum. The software used is the open source program MinimPy (http://minimpy.sourceforge.net/).

When a patient agrees to participate in the study they irrevocably receive a unique identification number, which cannot be changed or removed from the database. After completion of baseline measurements, treatment allocation is conducted through a central computerized allocation using the locked database for all participating centres. Then the physician and the patient are informed of the assigned condition and the treatment is planned. In this way, allocation concealment is guaranteed.

